## Methods

### Study design

PROSA is a monocenter, observational, prospective cohort study. 148 patients with chronic obstructive lung disease (COPD) stages 2–3, groups B and E according to GOLD [7] will be enrolled in this clinical study. We expect that one third of our study cohort will experience exertional hypoxemia based on incidence rates reported in previous studies [22, 23]. Patients will be recalled to the study site once per year for a total of 36 months of follow-up.

The primary endpoint of the study will be the difference in FEV_1_ (LLN) over time in COPD patients with exertional desaturation versus those without exertional desaturation (exertional desaturation will be defined as oxyhemoglobin saturation by pulse oximetry (SpO_2_) < 90% or a drop of SpO_2_ ≥ 4% during a six-minute walk test [19].

Secondary endpoints have been defined as follows: (1) The difference in all-cause mortality over time in COPD patients with exertional desaturation versus those without exertional desaturation. (2) The difference in COPD-related mortality over time in COPD patients with exertional desaturation versus those without exertional desaturation. (3) The difference in frequency of hospital admissions for exacerbation of COPD in COPD patients with exertional desaturation versus those without exertional desaturation. (4) The difference in frequency of hospital admissions for causes other than exacerbation of COPD in COPD patients with exertional desaturation versus those without exertional desaturation. (5) The sensitivity and specificity of plasma biomarkers at baseline to predict the prevalence of exertional desaturation in COPD patients. (6) The sensitivity and specificity of plasma biomarkers at baseline to prospectively predict the slope of lung function decline in COPD patients. (7) The sensitivity and specificity of plasma biomarkers at baseline to prospectively predict the mortality rate in COPD patients. (8) The difference in incidence and extent of exercise hypoxemia between carriers and non-carriers of single nucleotide polymorphisms in genes of the L-arginine – dimethylarginine pathway. (9) The difference in positive and negative predictive value of bicycle ergometry, 6-minute walk test, and 15-sec breath-hold test to discriminate between COPD patients with exertional desaturation versus those without exertional desaturation.

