### Determination of endpoints

#### Spirometric assessment of lung function

Lung function will be assessed by spirometry according to pneumological routine protocols. FEV_1_ and FVC will be recorded amongst other routine spirometric parameters and interpreted according to the latest edition of joint European Respiratory Society / American Thoracic Society Guideline on spirometry [24, 25] as the best values reached by a patient during three repeated spirometry runs on each clinical investigation to assess pulmonary function. FEV_1_ results will be analyzed against age- and sex-controlled normal ranges (LLN = lower limit of the normal range) [26], and their change between baseline investigation and the last investigation during follow-up of this study will be calculated to assess the percent change in FEV_1_ (percent of LLN), which is the primary end-point of the study.

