### Study conduct and funding

The PROSA study is exclusively being funded by the European Commission as part of the European Research Council Advanced Grant Project “NO PRESSURE” (Regulation of the L-Arginine – ADMA – Nitric Oxide (**NO**) Pathway in the **P**ulmonary Vascular **Res**ponse to Hypoxia and its Role for **Sur**vival of High-Risk COPD Pati**e**nts; Proposal NO. 101,096,706).

Patients who are selected by their primary physician or pulmonology specialist as suitable for participation in the study and who are willing to undergo screening for the study will be screened by the investigators according to the inclusion and exclusion criteria. Patients who fulfil the inclusion and exclusion criteria will be informed about the scope, aims, and possible risks of the study, and after having given their written informed consent, will undergo baseline investigation (study day 1).

Investigations on study day 1 will comprise peripheral venous blood sampling and capillary blood sampling, assessment of endothelial function by measuring flow-mediated vasodilation on the forearm by ultrasound, echocardiography, spirometry, and exercise testing. The total duration of these studies is estimated to take 2.5–3 h per patient.

After completing clinical investigations on study day 1, patients will be released into ongoing primary medical care. The second investigation (study day 2) will be scheduled at 12 months after the first study day, and additional studies will take place at 24 months (study day 3) and 36 months (study day 4) after the first study day. On each of these follow-up study days, patients will be asked about their health status during the preceding 12 months, with special focus, but not exclusively, on clinical symptoms and possible exacerbations of their COPD. Thereafter, the same clinical investigations as described for study day 1 will be repeated in identical manner. After the end of study day 4, i.e. at 36 months, the study will be completed for each patient.

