### Statistical analysis

Statistical analyses will be performed using the SPSS Version 27 software package (IBM Corporation, Armonk, NY, USA) and GraphPad Prism (version 6.01, GraphPad Software, San Diego, CA, USA) in the investigational center. All variables will be tested for normal distribution using the Kolmogorov–Smirnov test. Data will be expressed as mean with standard deviation (SD). Differences between groups will be tested for significance using the nonparametric Mann–Whitney U test for two groups or the Kruskal–Wallis analysis of variance for more than two groups. The Chi^2^ test will be used for comparison of categorical variables between groups. Logistic regression will be used to assess the relationship between exertional hypoxemia and mortality. The nil hypothesis for statistical evaluation of the primary endpoint will be that the difference in FEV_1_ (LLN) at 3 years of follow-up will not be different between COPD patients with exertional desaturation versus those without exertional desaturation. Exertional desaturation will be defined as oxyhemoglobin saturation by pulse oximetry (SpO_2_) < 90% or a drop of SpO_2_ ≥ 4% during a six-minute walk test [19].

Survival analyses will be performed using Kaplan–Meier curves comparing patients with or without exertional hypoxemia, and with ADMA and SDMA above or below the cut-off value determined in receiver-operated curve (ROC) analyses. Hazard ratios (HR) and 95% confidence intervals (CI) will be calculated by multivariable-adjusted logistic regression analyses. For all tests, *p* < 0.05 will be considered statistically significant. A correction of p will be performed for multiple comparisons when adequate.

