### Sample size discussion

Sample size estimation was based on analysis with repeated-measures 2-way ANOVA (baseline – 1 year – 2 years – 3 years). We assume that one third of our study cohort will experience exertional hypoxemia as reported in previous studies [22, 23], and we estimate that a 20% difference in the primary endpoint will be of clinical significance. To prove or dismiss the primary endpoint with α = 0.05 and a power of 0.90, a total sample size of 148 COPD patients stages 2–3, groups B and E according to the current GOLD guideline [7] will be included in this study after accounting for an expected drop-out rate of up to 15%.

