Clinical follow-up with classical spirometric lung function testing will allow us to address the primary endpoint of the study, i.e., the difference in decline of FEV1 expressed as percent of the lower limit of normal as published in [26] during follow-up between patients with and without exertional hypoxemia, respectively. This is a robust endpoint that is based on a ubiquitously available clinical method, ensuring that our results will be easily transferable into routine pneumological patient care. Beyond this, we will also analyze total mortality during follow-up and hospitalization rates for COPD exacerbation and for other causes as secondary clinical endpoints.

Aside from this, we will strive to better understand the pathophysiology linking exertional hypoxemia with progression of lung disease. We have evidence supporting a role for the pulmonary L-arginine – ADMA – NO pathway in modulating the response of the lung to intermittent hypoxia, and we will test in PROSA whether L-arginine-related metabolites may be suitable as biomarkers for differentiating COPD patients with and without exertional hypoxemia and/or COPD patients with good or poor prognosis, respectively. Biomarkers have become important clinical diagnostic tools that also help in therapeutic decision making. Thus, if the biomarkers we will analyze show predictive value for differentiating COPD patient subgroups, this may aid in risk assessment in clinical routine as well. Also, therapeutic intervention in this pathway has been tested by various means in other diseases; it may help to find more personalized treatments options for the subgroup of COPD patients with exertional hypoxemia and thus stimulate future therapeutic trials. The overall hypothesis for PROSA is depicted schematically in Fig. 3.

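### Secondary endpoint 6 sets sensitivity and specificity as the measure for a continuous outcome, the slope of lung function decline; a continuous marker-by-time analysis should be the main analysis.

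*Protocol article*

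**What the plan says.** The protocol article lists nine secondary endpoints under Study design. Endpoints 5 to 7 concern the accuracy of baseline plasma biomarkers. Endpoint 6 is "The sensitivity and specificity of plasma biomarkers at baseline to prospectively predict the slope of lung function decline in COPD patients".

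The lung function outcome is described on a continuous scale. Under Spirometric assessment of lung function, the change in FEV1 from baseline to the last visit "will be calculated to assess the percent change in FEV_1_ (percent of LLN), which is the primary end-point of the study". Spirometry is done at baseline and 12 months, and "additional studies will take place at 24 months (study day 3) and 36 months (study day 4) after the first study day" (Study conduct and funding), so a patient contributes at most four readings.

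The only cut-off from data in the Statistical analysis section is on the marker, for the survival curves: patients are compared "with ADMA and SDMA above or below the cut-off value determined in receiver-operated curve (ROC) analyses". In the Discussion the investigators hope that "if the biomarkers we will analyze show predictive value for differentiating COPD patient subgroups, this may aid in risk assessment in clinical routine".

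**The concern.** Sensitivity is the share of patients with the event whom the marker flags. Specificity is the share without the event whom it does not flag. Both need an event. Endpoint 5 has one, with stated thresholds ("exertional desaturation will be defined as oxyhemoglobin saturation by pulse oximetry (SpO_2_) < 90% or a drop of SpO_2_ ≥ 4% during a six-minute walk"), and endpoint 7 has death. Endpoint 6 has a slope, so its stated measure does not fit its stated outcome.

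To follow the endpoint, someone must estimate each patient's slope, choose a cut, and score the marker against the resulting label. Two costs follow. Cutting a continuous outcome gives up information, and the label inherits the error in each patient's slope. A marker that truly tracks decline could then look weaker than it is. The Background gives biomarkers of rapid progression as a study aim, and endpoint 6 is the one that links markers directly to decline.

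**Working it through.** **The plan's own figures.** The article gives no figure for endpoint 6. Its 148 patients are for the primary endpoint and cannot be reproduced, because no standard deviation (SD) accompanies the 20% difference. That number is used here only for the evaluable sample: 148 × (1 − 0.15) = 125.8, about 126.

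**Step 1: does the measure fit the outcome?**
- Endpoint 5: desaturation, yes/no, thresholds stated.
- Endpoint 6: slope of decline, continuous, no threshold stated.
- Endpoint 7: mortality, yes/no.
- Statistical analysis section: a cut on ADMA and SDMA, which is on the marker side and for survival.

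Nothing in the article turns the slope into two classes.

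**Step 2: information lost by cutting the slope.** For a normal outcome and a weak association, cut so that a share q lies above, the share of information kept is φ(z)² / [q(1 − q)], where z is the normal quantile at 1 − q.

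| Cut | z | φ(z) | Kept | Lost | 126 patients count as |
|---|---|---|---|---|---|
| Median (q = 1/2) | 0 | 0.399 | 0.637 | 36% | 80 |
| Top third (q = 1/3) | 0.431 | 0.364 | 0.595 | 41% | 75 |
| Top quarter (q = 1/4) | 0.674 | 0.318 | 0.539 | 46% | 68 |

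As an illustration, take a marker-slope correlation of 0.25 (assumed), n = 126 and two-sided α = 0.05. A correlation test has power Φ(atanh(0.25) × √123 − 1.96) = 0.81. In simulation, a Mann-Whitney test of the marker between the two slope classes has power of about 0.59 at a median cut and 0.55 for the top third.

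*Other distributions.* The efficiency of a median cut relative to a mean-based analysis is 4 f(0)² × variance:
- logistic: 0.82, a loss of 18%;
- t with 5 df: 0.96, a loss of 4%;
- t with 4 df: 1.13, no loss;
- Laplace: 2.0, no loss.

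**Step 3: noise in each patient's slope.** With visits at 0, 1, 2 and 3 years, the squared deviations of time from its mean sum to 2.25 + 0.25 + 0.25 + 2.25 = 5. The error variance of a fitted slope is therefore σ²/5. Reliability is s² / (s² + σ²/5), where s is the SD of true slopes and σ the visit-level error SD. For a marker that knew every true slope, with both variables cut at the median, sensitivity = specificity = 1/2 + arcsin(√reliability)/π.

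The article gives neither SD. The assumed ranges are s = 20 to 60 mL/year and σ = 50 to 150 mL.
- s = 20, σ = 150: reliability 400/(400 + 4500) = 0.08, ceiling 0.59.
- s = 40, σ = 100: reliability 1600/(1600 + 2000) = 0.44, ceiling 0.73.
- s = 60, σ = 50: reliability 3600/(3600 + 500) = 0.88, ceiling 0.89.

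Using only the baseline-to-last change divided by 3 years (error variance 2σ²/9) moves the ceiling little, to 0.59, 0.72 and 0.88. With no measurement error it is 1.00 at any cut.

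**The case against.** The strongest reply is that only a number is missing. The article speaks of rapid and slow progression and of good and poor prognosis, so endpoint 6 can be read as classifying rapid decliners. A journal article may leave the threshold to the full protocol or analysis plan, neither of which is shown. Classification also suits the screening use the authors have in mind. This stands in part. The absence of a threshold from the article is not itself a fault, and sensitivity and specificity have a place. But the article does fix the measure, and a threshold elsewhere would make it computable without recovering what the cut discards.

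A reader might go further in four ways that the documents do not support.
- *At least 36% is always lost.* That figure needs near-normal slopes, a weak association and a median cut. The article gives no slope distribution, and heavy tails reduce or remove the loss.
- *The cut caps a perfect marker well below 1.* The cap comes from measurement error, under SDs assumed here in mL, whereas the outcome is percent of LLN. Such noise would also lower a correlation or R-squared.
- *The cut is arbitrary or chosen after the slopes are seen.* No text says so; it may be fixed in a document not shown.
- *A good marker will be dropped.* The article states no rule for dropping markers.

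**Conclusion.** The point holds as a mismatch between measure and outcome in one secondary endpoint. As worded in the article, endpoint 6 cannot be computed. With a cut, using classification alone costs about 36% to 46% of the information for cuts between the median and the top quarter, if slopes are near normal and the association weak. Slope noise is a separate limit. Over the assumed SDs it holds even a perfect marker of the true slope to roughly 0.6 to 0.9 at a median cut, and the width of that range reflects how little the article says about variability. Endpoints 5 and 7 and the primary comparison are not touched. The change is worth making because a better analysis is available from the same data at little cost.

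**What to change.** Reword endpoint 6 so that its main analysis is the association of each continuous baseline biomarker (log-transformed, per SD) with the rate of decline in FEV1 (percent of LLN). Estimate it as the biomarker-by-time term, with a 95% confidence interval, in a linear mixed model with random intercept and slope, using all four visits. Visit-level error in FEV1 then widens the interval but does not bias this term.

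Three details matter:
- Do not enter baseline FEV1 as a covariate while it is also one of the responses.
- Enter any adjustment covariates that the study collects, such as age and sex, together with their interactions with time; otherwise they do not adjust the slope. The article does not mention recording smoking, so do not assume it is available.
- Report adjustment for walk-test desaturation only as a separate added-value analysis, because the endpoint asks whether the marker predicts decline, not whether it adds to the walk test.

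Keep sensitivity and specificity as descriptive figures against one definition of rapid decline, fixed before slopes are seen. If the full protocol or analysis plan already has such a definition, cite it.

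The cost is the wording of one secondary endpoint and one extra model, which the named software (SPSS) can fit, with no new visits or measurements. The downside is that the headline becomes a difference in slope per SD of the marker, which is less familiar to clinicians than a sensitivity.

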**Methods:**

148 COPD patients (GOLD stage 2–3, groups B or C) will undergo exercise testing with continuous pulse oximetry. They will be followed for 36 months by spirometry, echocardiography, endothelial function testing, and biomarker analyses. Exercise testing will be performed by comparing the 6-min walk test (6MWT), bicycle ergometry, and a 15-sec breath-hold test. Exertional desaturation will be defined as SpO_2_ < 90% or delta-SpO_2_ ≥ 4% during the 6MWT. The primary endpoint will be the rate of decline of FEV1(LLN) between COPD patients with and without exertional desaturation.

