**Discussion:**

The PROSA Study is an investigator-initiated prospective study that was designed to prove or dismiss the hypothesis that COPD patients with exertional desaturation have a significantly more rapid rate of decline of lung function as compared to non-desaturators. A 20% difference in the primary endpoint was considered clinically significant; it can be detected with a power of 90%. If the primary endpoint will be met, exercise testing with continuous pulse oximetry can be used as a ubiquitously available, easy screening tool to prospectively assess the risk of rapid lung function decline in COPD patients at an early disease stage. This will allow to introduce personalized, risk-adapted therapy to improve COPD outcome in the long run. PROSA is exclusively funded by public funds provided by the European Research Council through an ERC Advanced Grant. Patient recruitment is ongoing; the PROSA results are expected to be available in 2028.

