**Fig. 2 Fig2:**
[figure not shown]
Intermittent hypoxemia, as caused by co-morbid obstructive sleep apnea, has been shown to act as a driver of rapid lung function decline, systemic cardiovascular co-morbidity, and excess mortality. Exercise is another well-known trigger of intermittent, exertional hypoxemia. Previous research has revealed that hypoxia causes dysregulation of the endothelial L-arginine – dimethylarginine – nitric oxide pathway, causing excess hypoxic pulmonary vasoconstriction. We hypothesize that dysregulation of this important pulmonary vascular signalling pathway also affects the rate of decline of lung function and, by spillover of dimethylarginines from the pulmonary into the systemic circulation, triggers systemic co-morbidities, and thereby contributes to poor prognosis

The PROSA study sets out to investigate, by three different means, the prevalence of exertional desaturation in COPD patients at a relatively early stage. The 15-sec breath-hold test has been described to unveil sensitivity of COPD patients to intermittent hypoxemia [20]; it is an easily feasible and versatile test in clinical practice. The six-minute walk test certainly is the most often used exercise test in chronic diseases; it has been reported to generate a reliable diagnostic yield for exertional desaturation when continuous recording of SpO_2_ is performed [19]; therefore, it was selected as the primary determinant for stratification of COPD patients with or without exertional hypoxemia in the PROSA Study. Step tests on a bicycle ergometer cause the most effort in terms of personnel and equipment; however, this procedure can be expected to generate the best reproducibility of results; ergometer step tests have been shown to allow detection of exertional desaturation with continuous SpO_2_ recording in COPD patients [21]. In PROSA, all three approaches will be compared for their diagnostic sensitivities and specificities.

Non-invasive methods for assessing cardiac function, estimating pulmonary arterial pressure, and measuring systemic endothelium-mediated vasodilation will be applied to better understand the hemodynamic and vascular functional differences between COPD patients with and without exertional desaturation. This will be accompanied by biomarker measurements in blood samples taken throughout the study’s follow-up period of three years, allowing to keep a closer eye on the underlying biochemical mechanisms.

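### Secondary endpoint 9 judges the 6-minute walk test against a reference defined by the same walk test, so it cannot rank the three desaturation tests

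*Protocol article*

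**What the plan says.** All places are in the Protocol article.

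- **Endpoint 9 (Methods, Study design).** The endpoint is "The difference in positive and negative predictive value of bicycle ergometry, 6-minute walk test, and 15-sec breath-hold test to discriminate". What the tests are to tell apart is the presence or absence of desaturation on exertion. The 6MWT is one of the three tests listed.
- **Definition of the target condition.** The Abstract (Methods) has "Exertional desaturation will be defined as SpO_2_ < 90% or delta-SpO_2_ ≥ 4% during the 6MWT". Study design repeats it, with "a drop of SpO_2_ ≥ 4% during a six-minute walk test" as the second criterion. Statistical analysis gives the same two criteria, again "during a six-minute walk test".
- **Role of the 6MWT (Discussion).** Of the 6MWT the article says that "it was selected as the primary determinant for stratification of COPD patients with or without exertional hypoxemia in the PROSA Study".
- **Restatement of the comparison (Discussion).** "In PROSA, all three approaches will be compared for their diagnostic sensitivities and specificities".
- **Purpose (Methods, Assessment of exertional hypoxemia).** The article says that all three procedures have been used before in COPD patients, but that their diagnostic usefulness has not yet been compared head to head. It presents the comparison as something PROSA will add.

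No section names a separate or composite reference for endpoint 9.

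**The concern.** Comparing diagnostic tests requires a reference that is not itself one of the tests. Here the reference is the 6MWT result, and the 6MWT is also a competitor. Its row in the results table is fixed before any patient is enrolled.

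The other two rows are affected as well. A patient who desaturates on ergometry but not on the walk counts as a false positive for ergometry, and a patient who desaturates only on the walk counts as a false negative. Neither disagreement can count against the 6MWT. A reader of the results could conclude that the walk test is the best of the three when the data had no means of showing otherwise.

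**Working it through.** **Inputs.** The index tests are ergometry, 6MWT and breath-hold (Study design, endpoint 9). The target condition is exertional desaturation as defined by the 6MWT (Abstract, Study design, Statistical analysis). The expected prevalence is p = 1/3 (Study design; Sample size discussion). The article gives no accuracy figure for endpoint 9, so there is none to reproduce.

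**Step 1: the identity.** Write W for the 6MWT result and D for the target condition. By the stated definition D+ holds exactly when W+ holds. Then

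- sensitivity = P(W+ | D+) = 1 and specificity = P(W− | D−) = 1;
- PPV = Se·p / [Se·p + (1 − Sp)(1 − p)] = (1/3) / (1/3 + 0) = 1;
- NPV = Sp(1 − p) / [Sp(1 − p) + (1 − Se)p] = (2/3) / (2/3 + 0) = 1.

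The result is the same at every prevalence strictly between 0 and 1 and needs no assumed figure. No other test can exceed 1, so the other two can only tie or lose.

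**Step 2: what this does to the ranking.** This step is an illustration, and its accuracies are assumptions. Suppose a true desaturation status exists with p = 1/3. Let the 6MWT have true Se = Sp = a and ergometry true Se = Sp = b, with independent errors given the true status. Judged against the 6MWT, ergometry shows

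- apparent PPV = [p·a·b + (1 − p)(1 − a)(1 − b)] / [p·b + (1 − p)(1 − b)];
- apparent NPV = [p(1 − a)(1 − b) + (1 − p)·a·b] / [p(1 − b) + (1 − p)·b].

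Worked case, a = b = 0.85:

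- PPV = (0.2408 + 0.0150) / (0.2833 + 0.1000) = 0.667
- NPV = (0.0075 + 0.4817) / (0.0500 + 0.5667) = 0.793

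| 6MWT true Se = Sp | Ergometry true Se = Sp | True PPV / NPV, 6MWT | True PPV / NPV, ergometry | Reported PPV / NPV, 6MWT | Reported PPV / NPV, ergometry |
|---|---|---|---|---|---|
| 0.85 | 0.85 | 0.739 / 0.919 | 0.739 / 0.919 | 1.00 / 1.00 | 0.667 / 0.793 |
| 0.90 | 0.95 | 0.818 / 0.947 | 0.905 / 0.974 | 1.00 / 1.00 | 0.824 / 0.879 |
| 0.85 | 1.00 | 0.739 / 0.919 | 1.000 / 1.000 | 1.00 / 1.00 | 0.850 / 0.850 |

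In the first row two equally good tests are reported as unequal. In the second and third rows the better test is reported as the worse one. With error-free ergometry, its reported PPV and NPV both equal a. Over a = 0.80, 0.85, 0.90 and 0.95 they are 0.80, 0.85, 0.90 and 0.95, against a true value of 1.00.

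If the two tests tend to err in the same patients, ergometry's reported values rise and may even exceed its true ones. They still cannot pass the 6MWT's 1.00. The size of the distortion depends on these assumptions; the ceiling in step 1 does not.

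**The case against.** **The choice of reference is reasoned.** The Discussion justifies the 6MWT by its widespread use and its reported diagnostic yield with continuous SpO2 recording. Taking it as the reference is legitimate, and ergometry and breath-hold can still be estimated against it. All of this stands. The fault lies in also listing the 6MWT among the tests compared, and in presenting the result as a comparison of all three.

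**The intention may be to judge only the other two.** That would be sound, but endpoint 9 names the 6MWT and the Discussion says all three will be compared. A different 6MWT cut-off, or a repeat walk at a later visit as the index result, could bring its score below 100%. The article states neither, and the reference would still come from the same kind of test.

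**The consequences are limited.** This is the last of nine secondary endpoints in an observational cohort. It drives neither the sample size nor the grouping for the primary analysis. This also stands and limits the severity.

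**Stronger readings that the article does not support.**

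- A reader might infer that ergometry should be the reference, because the Background ranks it highest for exercise testing. That remark is about exercise testing in general. Nothing makes ergometry the reference for desaturation.
- A reader might see a conflict between predictive values in Study design and sensitivity and specificity in the Discussion. These are complementary summaries of the same two-by-two table. The wording is loose but not contradictory.
- A reader might extend the point to the Abstract's statement "If the primary endpoint will be met, exercise testing with continuous pulse oximetry can be used as a ubiquitously available, easy screening tool". That statement depends on the primary endpoint, not on endpoint 9, and is a separate question. The article also gives no basis for putting a figure on screening accuracy: the Sample size discussion states a 20% difference without a standard deviation.

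**Conclusion.** The point holds for endpoint 9 and its restatement in the Discussion. On the only definition printed, the 6MWT scores 100% on all four accuracy measures by identity, and the three-way comparison cannot show another test to be better. This assumes only that the index result and the reference are the same walk test at the same threshold, which is the sole reading the text offers. The ergometry figures in the table rest on assumed accuracies and independent errors, and show the direction of the problem rather than a forecast.

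It should be fixed, but it does not threaten the study. The primary endpoint is unaffected, and the agreement of ergometry and breath-hold with the 6MWT remains estimable.

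**What to change.** **Sufficient change.** Reword endpoint 9 so that the 6MWT is named as the reference and no longer listed as an index test. Report sensitivity, specificity, PPV and NPV of ergometry and of breath-hold against it, with kappa for agreement and McNemar's test for a difference in the proportion classified as desaturating. State that these results measure agreement with the 6MWT and cannot show that any test is superior to it. Align the Discussion sentence on comparing all three approaches, and the head-to-head statement under Assessment of exertional hypoxemia. The cost is wording and analysis text only, since all three tests are already performed.

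**Optional addition, if a ranking of all three is wanted.** Compare the three baseline tests against an outcome independent of them that is already collected, such as FEV1 decline over 36 months, using paired comparisons because each patient has all three tests. This asks a prognostic question rather than a diagnostic one, so it should stand beside the agreement analysis and not replace it.

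The price is precision. If the fastest-declining third were the target (an assumption), there would be about 42 to 49 such patients: 126/3 = 42 after 15% drop-out (148 × 0.85 ≈ 126), and 148/3 ≈ 49 without drop-out. At a sensitivity of 0.5 the 95% half-width is 1.96 × √(0.25/42) ≈ 0.15 to 1.96 × √(0.25/49) = 0.14.

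Recruitment is ongoing and results are expected in 2028, so either change can be made before analysis.
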